3.1. Inclusion criteria

(i) histologically diagnosed gastric cancer via endoscopic biopsy or surgical specimen retrieval; (ii) suspected PM/recurrence of gastric cancer based on at least one of the following clinical findings: abnormal physical symptoms with causes that could not be explained by other diseases, elevation of serum tumor markers, and suspicious but not definitive signs of PM on conventional CT images; (iii) Eastern Cooperative Oncology Group (ECOG) performance status of 0, 1, or 2; (iv) oral intake ability; and (v) provision of written consent by each patient.

3.2. Exclusion criteria were

(i) inability to undergo bowel preparation; (ii) obvious intestinal stenosis; (iii) presence of massive ascites; and (iv) inability to undergo carbon dioxide (CO2) insufflation through the rectum.

4. Registration

5.1. Standardized procedure

5.1.1. Preparation

Bowel preparation was performed by administering low-residue diets for the three meals on the day before CTC, along with oral administration of a laxative (50 g magnesium citrate diluted in 180 mL of water and 10 mL of 0.75% sodium picosulfate) at 3:00 PM on the same day.

5.1.2 CTC

1.After the colon was inflated with sufficient CO2 through a rectal catheter with the patient in the left lateral decubitus position.

2.CTC of the abdominal cavity was performed in the supine and side positions. The procedure was repeated in the prone position.

3.All patients underwent the same process to ensure the reproducibility of CTC.

5.2. Interpretation

Radiological interpretations regarding abnormal deformity and/or thickness of the colonic wall were made by the attending surgeons and radiologists.

6. Predicted adverse events

Along with the procedure of CTC, adverse events such as gastrointestinal perforation, gastrointestinal bleeding and bleeding will be dealt appropriately whenever occurred.

7. Ethical matters

All researchers involved in this study act in conformity to the principles of the Helsinki Declaration (http://www.med.or.jp/wma/) and the Japanese Ethical Guidelines for Clinical Studies(http://www.mhlw.go.jp/topics/2003/07/tp0730-2.html).

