0.1. Schema

Advanced Gastric cancer or

postoperative cases suspicious for recurrence

・Suspicious of PM: 1 to 3 of following three clinical criteria

1) Symptoms

Pain, Abdominal distention, Nausea, Tenesmus

2) Tumor marker

Elevation of CEA and/or CA19-9 and/or CA125

3) Images

Ascites, Thickness of intestinal wall and/or intestinal mesentery.

・ECOG performance status : 0/1/2

・ No bowel obstruction

・ Written Informed consent

CT colonography

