0.2. Aim

CTC will be performed aiming at improvement of diagnostic performance in patients in whom peritoneal metastasis/recurrence of stomach cancer is suspected based on physical, laboratory test, and imaging findings, but no definite diagnosis can be made. The presence or absence of deformation suggesting peritoneal dissemination in the large intestinal wall will be diagnosed jointly by the physician in charge and radiologist and correlation with the clinical course will be analyzed.

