2.3. Study design

2.3.1. Endpoint

The primary endpoint of this study was the diagnostic sensitivity of CTC for PM. The secondary endpoints included overall survival (OS) and progression-free survival (PFS). The diagnostic sensitivity of CTC has been estimated to be 60%, with a threshold value of 50% and an expected value of 75%. Using Simon’s two-stage method with a one-sided alpha value of 0.05 and a beta value of 0.7, we determined that a sample of 18 patients was required for this study.

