7.1. Explanation and acquisition of written consent

The attending surgeon provided the oral explanation by using the document approved by the ethic screening committee (or Institutional Review Board，IRB) before registering, and obtain an agreement by the free will of the person with written consent. When a study cooperator gives a supplementary explanation other than the medical attendant whom explained, a signature seals it after filling out each date or the study cooperator concerned signs written consent and a signature seals the person of object after filling out an agreement day or signs it. The copy of written consent will be provided to the patient and the original will be kept in facilities.

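### The only CTC result behind the primary sensitivity endpoint is a joint reading that includes the treating physician, so it measures CTC plus clinical information and probably overstates CTC itself.

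*Protocol*

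**What the plan says.** Section 2.3.1 defines what is measured: "The primary endpoint of this study was the diagnostic sensitivity of CTC for PM". The sample size is built on that quantity, "with a threshold value of 50% and an expected value of 75" per cent.

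Two places say who produces the CTC result. Section 5.2 states that interpretations of abnormal deformity or thickness of the colonic wall "were made by the attending surgeons and radiologists". Section 0.2 states that the presence or absence of such deformity "will be diagnosed jointly by the physician in charge and radiologist", and that its correlation with the clinical course will then be analysed. No separate radiologist reading is described. Nothing is said about what the readers may know, and no threshold is given for calling a wall abnormal.

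Patients enter because of "suspected PM/recurrence of gastric cancer based on at least one of the following clinical findings", namely symptoms, raised tumour markers or a suspicious conventional CT (section 3.1). The schema in section 0.1 shows that the strength of suspicion differs between patients: "Suspicious of PM: 1 to 3 of following three clinical criteria". Section 7.1 places the attending surgeon with the patient before registration: "The attending surgeon provided the oral explanation".

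**The concern.** A sensitivity attributed to an imaging test should come from what the reader sees on the images. Here one of the two readers is the treating physician of a patient who was enrolled because other findings already pointed to PM. If those findings enter the reading, the result mixes CTC with the clinical picture.

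Three features make this matter.

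- The sign is a judgement about wall deformity or thickening with no cut-off, so equivocal scans leave room for interpretation.
- Suspicion ranges from one to three criteria. A reader who knows the count can lean towards positive in the patients with the most criteria. If the count tracks PM, that raises apparent sensitivity.
- Sensitivity is the only accuracy measure named as an endpoint, so calling more scans positive carries no visible penalty.

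What is at stake is the primary conclusion: CTC could be declared better than 50% partly because of information that was available without it.

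**Working it through.** **1. Reading conditions, side by side.**

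| Question | Protocol text | Section |
|---|---|---|
| What is estimated? | Sensitivity of CTC for PM | 2.3.1 |
| Who makes the call? | Attending surgeons and radiologists, jointly | 5.2, 0.2 |
| What qualifies the patient? | At least one of symptoms, markers, conventional CT | 3.1 |
| Does suspicion vary? | Yes, one to three criteria | 0.1 |
| Has the attending surgeon dealt with the patient before CTC? | Yes, explains the study and obtains consent | 7.1 |
| Masking, or a separate radiologist call? | None described | 5.2 |

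That the attending physician knows the entry findings is an inference, but a firm one.

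**2. The plan's own sample size.** Inputs from section 2.3.1: p0 = 0.50, p1 = 0.75, and "one-sided alpha value of 0.05 and a beta value of 0.7". The 0.7 gives 18 patients only if read as power 0.70; read literally as beta (power 0.30), a two-stage search gives N = 7. With power 0.70, an exact binomial search returns:

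- Minimax Simon design: stop if 3 or fewer of the first 7 are positive; succeed if more than 12 of 18 are positive. Alpha 0.0464, power 0.706.
- Single-stage design: n = 18, succeed with at least 13 positive. Alpha 0.0481, power 0.717.

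So 18 is reproduced and the arithmetic of the sample size is not in dispute. The protocol states neither decision rule; both are reconstructions.

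**3. Effect of an upward shift.** The protocol gives no size for the bias, so the shift d is assumed. It is also assumed that all 18 patients have PM, since sensitivity is computed only in patients with PM. CTC's own sensitivity is set at the 50% threshold and the apparent sensitivity is p = 0.50 + d.

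Single-stage: P(success) = P(X ≥ 13), X ~ Binomial(18, p).

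Two-stage: P(success) = Σ over x = 4 to 7 of P(X1 = x) × P(X2 ≥ 13 − x), with X1 ~ Binomial(7, p) and X2 ~ Binomial(11, p).

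| Assumed shift d | Apparent sensitivity p | Single-stage, ≥13/18 | Minimax Simon, 3/7 and 12/18 |
|---|---|---|---|
| 0 | 0.50 | 4.8% | 4.6% |
| 5 points | 0.55 | 10.8% | 10.4% |
| 10 points | 0.60 | 20.9% | 20.3% |
| 15 points | 0.65 | 35.5% | 34.6% |

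A 5-point shift roughly doubles the false-success rate (10.8 / 4.8 ≈ 2.2), and a 10-point shift roughly quadruples it (20.9 / 4.8 ≈ 4.3). With 18 patients one call is 1/18 = 5.6 points of sensitivity, and a single call moved from negative to positive takes 12 of 18 (not a success) to 13 of 18 (a success).

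**The case against.** The strongest reply is that an informed joint reading is the stated design. CTC is an added examination in patients already suspected of PM but not yet diagnosed, section 0.2 puts the joint reading into the aim, and in practice such a scan would be read with the clinical picture at hand. The protocol never uses the phrase CTC alone. This has force: a masked reading answers a somewhat different question, which is why the joint reading should be kept. It does not remove the mismatch, because section 2.3.1 names the result, and tests it against 50%, as the sensitivity of CTC.

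A second reply is that every patient enters under suspicion, so knowing of it cannot separate one patient from another. That would hold if suspicion were uniform. The schema allows one, two or three criteria, so selective leaning is possible, and a generally lower threshold for calling a scan positive would also raise sensitivity. The protocol does not show that the number of criteria tracks PM.

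Three stronger readings are not supported.

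- A reader might infer that scans were read after the outcome was known. The protocol is silent on recording and locking, and silence does not establish late reading. Section 0.2 places the CTC diagnosis before its correlation with the course, and section 1 aims at early detection and timely treatment, which implies a prompt reading.
- A reader might infer that the attending physician also selects the patient and adjudicates the outcome. Section 3.1 names no selector and section 0.2 names no adjudicator.
- A reader might take the remark on objectivity and reproducibility in section 2.2.4 as a claim of reader agreement that this design contradicts. It is background about CTC images as a technique that can be standardised.

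**Conclusion.** The point holds as a mismatch between the primary endpoint and the reading conditions fixed for it. As written, the primary result will be the sensitivity of CTC combined with whatever clinical information the treating physician brings. Upward bias is likely; its size is unknown and cannot be derived from the protocol.

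The false-success figures (about 5% without bias, about 10% to 35% for assumed shifts of 5 to 15 points) show how sensitive a study of 18 patients is to a modest shift. They do not estimate the bias. They rest on the assumed shifts, on all 18 patients having PM, and on decision rules reconstructed from the design parameters. Patients are enrolled on suspicion, so the true denominator may be below 18. The single-stage and two-stage rules agree closely, so the choice between them does not drive the message.

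This should be changed; it does not by itself invalidate the study.

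**What to change.** In section 5.2, define the primary CTC result as the radiologist's own positive or negative call. It is recorded before discussion with the attending surgeon and before follow-up, and made without the symptoms, marker values or entry CT report. Keep the joint reading as a secondary result, so that the informed reading of section 0.2 is still reported.

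Cost: one extra form. A radiologist already reads the scans, so no new reader or procedure is required. The price is a possibly lower sensitivity and less resemblance to routine informed reading.

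Masking will be incomplete. The CTC covers the abdominal cavity (section 5.1.2) and may itself show ascites or thickening, and the same radiologist may have read the entry CT; the protocol does not say. The change still takes the treating physician's knowledge out of the primary call.

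If the joint reading is to stay primary, the minimum is to relabel the endpoint as the sensitivity of CTC read with clinical information. That corrects the label but leaves the influence of the entry findings in place.

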7.1. Explanation and acquisition of written consent

The attending surgeon provided the oral explanation by using the document approved by the ethic screening committee (or Institutional Review Board，IRB) before registering, and obtain an agreement by the free will of the person with written consent. When a study cooperator gives a supplementary explanation other than the medical attendant whom explained, a signature seals it after filling out each date or the study cooperator concerned signs written consent and a signature seals the person of object after filling out an agreement day or signs it. The copy of written consent will be provided to the patient and the original will be kept in facilities.

7.2. Privacy and patient identification

When handling the data and consent forms related to the implementation of the research, sufficient consideration will be given to protecting the confidentiality of the subjects. In addition, when preparing reports to be submitted outside the hospital, the subjects will be identified by the "case registration number" issued at the time of registration allocation and the "subject identification code" set within the facility, and confidentiality will be protected. The data obtained in this study will be used only for the purpose of this study.

7.3. Approval by the Institutional Review Board

Prior to the initiation of this study, each institution must submit the required documentation and be approved for participation in the study by an expedited review of the institution's IRB or other means.

7.4. Conflict of interest

There is no conflict of interest related to this study.

8.Research facility

